### Process evaluation

A process evaluation will assess the fidelity of intervention delivery calculating reach and dose and will document the views of participants about what worked well and what could be improved if we proceed to a larger trial. In addition, it will collect information about the context, facilitators and barriers to delivering the intervention.^54^ The process evaluation will include observations of the training for the health visitor and nursery staff and meetings between the NAP SACC UK Partner and each of the childcare providers. Nursery managers and NAP SACC UK Partners will be asked to complete logs of meetings including goals set, support given and progress made, and for the managers, changes made and reflections on these changes. Semistructured interviews will be conducted with all nursery managers in the providers, a sample of nursery staff, the NAP SACC UK Partners and sufficient numbers of parents until saturation is reached.

The home component will be evaluated with respect to use of the website and Facebook group, goal setting, text messages and emails using reports from the website and via semistructured interviews with parents who have different levels of engagement with the home component (none, low and high).

### Ethics and dissemination

Any protocol modifications will be submitted for ethics approval. Written informed consent will be obtained for all participants. As the effectiveness and cost-effectiveness of the intervention in the UK are unknown, we believe randomising participants to the intervention or usual care is warranted. All data will be held securely in accordance with Data Protection Regulations. Participant confidentiality will be maintained at all times. Findings will be widely disseminated in peer-reviewed journals, at conferences and to public health commissioners. Participants in the trial phase will be offered the option to receive a summary of the results once the study is complete.

### Sample size

The sample size for this feasibility study was not informed by a power calculation. The choice of 12 nurseries will provide some information on variability within and between nurseries at baseline and follow-up. This sample will not provide a usefully precise estimate of the intervention effect. However, the sample will indicate the likely response rates and intracluster correlations (ICCs) in anticipation of a larger trial. We will also use information on effect sizes and ICCs from other adequately powered diet, physical activity and obesity prevention trials to inform any calculation for a future phase III trial.

### Data management

Data will be entered and transcribed by the research staff using a secure data management system at the University of Bristol. Completed questionnaires will be transported to the University of Bristol by the study manager or the recruited fieldworkers. Data from questionnaires will be stored in anonymised form, using participant identification numbers. Participant identification numbers and corresponding participant names will be held in separate files. Both files will be stored in secure password-protected folders. Individuals' names will be replaced with pseudonyms in interview/focus group transcripts. A list of participant names, pseudonyms and their unique identification number will be held securely in a separate location. Digital recordings of interviews/focus groups will be stored securely and will be held separately from transcripts and information on participant identities.

### Analysis

The statistical analyses for this feasibility study will be primarily descriptive, providing realistic estimates of eligibility, recruitment, intervention delivery and retention rates in the study population, with 95% CIs calculated to incorporate between-provider variation where appropriate. The CONSORT flow diagram for clinical trial reporting will be completed. Summary statistics will also be presented for the outcome measures using means and SDs by allocation arm and key demographic variables as these will also inform the sample size and recruitment plan for the main trial. Differences will be explored for each of these measures by study location (North Somerset/Gloucestershire) and deprivation (high vs low). Comparisons will be made between those who complete the study and those who drop out to investigate if this is a potential source of bias. Missing data will not be imputed for the purposes of the feasibility study. However, the extent of missing data will be examined and described to inform the full trial. Stata statistical software will be used for all analyses.

We do not plan an economic evaluation alongside this feasibility trial. Our aim is to pilot measures of resource use and estimate more precisely the cost of the intervention to inform a full-scale trial. Costs and outcomes will be presented in a cost-consequence table. We will delineate the resource use (eg, h), unit costs (eg, cost/h) and calculate mean, provider and parental costs in the intervention and control groups. We will estimate incremental costs and 95% CIs for descriptive purposes.

For the qualitative analysis, all interview recordings will be transcribed verbatim and anonymised. As the data are exploratory, we will adopt a thematic analytical approach. Meaningful content will be coded and codes grouped to form themes that describe the content of codes. Quotations which best represent the nature of each theme will then be extracted.

## Discussion

This paper describes the protocol for the NAP SACC UK feasibility trial, which is attempting to improve the nursery environment and health of children aged 2–4 years with respect to nutrition, oral health, physical activity and sedentary time. Many young children in the UK do not achieve national standards for nutrition, oral health or physical activity and, upon entry to primary school, overweight and obesity are prevalent. Childcare settings are increasingly important in the UK with 15 h/week provided free for children aged 3–4 years and the intention is to increase this to 30 h/week for children in England by 2017.^55^ Given the lack of effective interventions to increase physical activity and healthy eating in young children, and the small number of trials which have been conducted in childcare settings in the UK, this study will provide important information to inform research and practice. The goal of this feasibility trial is to assess the potential of this intervention, developed and used successfully in the USA, to be adapted for use in the UK, expanded to involve parents and to provide all the information necessary to design a cluster RCT in UK childcare settings.

### Trial status

The current study status (26 January 2016): we have obtained ethical approval for the study, funding for the study and have recruited all project staff. Nursery and child recruitment began in August 2015 and baseline data collection started in September 2015 and will be completed by mid-February 2016. NAP SACC UK Partner training took place in December 2015 and January 2016 and the intervention will start in February 2016. At the inaugural meeting of the TSC, it was agreed that a data monitoring committee was not necessary as there were no safety concerns associated with implementing NAPSACC UK and no interim analyses were planned.

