Childcare settings provide opportunities to deliver interventions at the population level.^7^ Around 97% of children aged 3–4 years in England attend some form of government-funded early years education, of which 39% attend day care outside school settings.^8^ However, not all childcare settings are health-promoting environments. Assessment of physical activity in children aged 3–5 years at childcare in the USA has shown that children spend only 3% of time engaged in moderate-to-vigorous physical activity (MVPA).^9^ A study in England found that 593 children aged 4 years with valid accelerometer data met national guidelines for physical activity. However, this was mainly a light level of activity and children who attended nursery full time were more sedentary and less active in the mornings, with no differences in the rest of the day, compared with children who attended part time.^10^ The findings in this study contrast with other studies internationally which find young children not meeting national guidelines. This may reflect differences in the populations studied, as well as methods of data collection and analysis.^10^ As MVPA is closely associated with cardiorespiratory fitness and body mass index (BMI) in adolescence,^11^ it is of concern that such a small proportion of time in childcare is spent in MVPA. Further, around 80% of time at childcare is spent in sedentary activities.^9^ Childcare settings can be a strong predictor of physical activity levels and being outdoors is one of the most powerful correlates of physical activity in children.^9^ In addition, suitability of indoor play space and carer encouragement of indoor play are also predictors of MVPA.^12^ The lack of MVPA in childcare settings may be influenced by constraints of space, lack of equipment, lack of scheduled times for free play and outdoor play. A systematic review of interventions to increase physical activity in childcare settings found that regularly provided, structured physical activity programmes can increase the amount and intensity of physical activity.^13^

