#### Outcomes

For the purposes of this feasibility study, the primary outcomes are the acceptability of the intervention and the trial methods. The secondary outcomes will be measured at baseline (T0), prior to the intervention and 8–10 months after the baseline (T1). Multiple visits will be made to nurseries to maximise participant retention. Assessment of the secondary outcomes will inform the choice of primary outcomes for a full-scale trial. Further, it will inform whether the outcomes require data collected from parents/children, or if the outcomes could be the environmental audit and child zBMI obtained using anonymised data linkage with the National Child Measurement Programme. The secondary outcomes to be measured will include:

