*Environment and Policy Assessment and Observation (EPAO) instrument score*: The EPAO instrument assesses childcare nutrition and physical activity environments, policies and practices and was developed using the standards, recommendations and research literature upon which the NAP SACC intervention itself was based.^31^ It has been tested for validity and reliability in nursery settings in the USA.^38^ The EPAO consists of a 1-day observation and review of pertinent centre childcare settings' documents using 189-item questions and 16 free-text sections, with the average of all subscale scores representing total nutrition and physical activity scores. The EPAO has been adapted for use in nurseries in the UK and is administered by a researcher trained by a member of the US NAP SACC research team and blind to childcare provider allocation.*Anthropometric measures of children:* zBMI and proportion of overweight and obese, as determined by the UK 1990 age and gender reference charts at 85% and 95% centiles, respectively^39^, with further sensitivity analysis using the International Obesity Task Force thresholds^40^ to facilitate international comparisons. zBMI has been demonstrated to be a good measure of change in childhood adiposity.^41^ All anthropometric measurements will be completed with children with one trained fieldworker and a member of nursery staff present. Weight will be measured without shoes in light clothing to the nearest 0.1 kg using a Seca digital scale. Height will be measured, to the nearest 0.1 cm, without shoes, using a portable Harpenden stadiometer. All measurements will be repeated and the mean measurement used. Fieldworkers will be trained to ensure correct position for height assessment.*Accelerometer-measured activity* (mean minutes of sedentary, light, moderate and vigorous activity per day). We will use ActiGraph GT1M accelerometers which have been described as ‘the most widely used and extensively validated accelerometers for assessment of physical activity among children’.^42^ Accelerometers will be worn for 5 days including week and weekend days. Periods of 60 min with zero values will be interpreted as time that the monitor is not worn.^43^ A day will be considered valid if 8 h of data are recorded.^44^ Mean minutes of sedentary time (using two thresholds of 0–25 and 0–199 counts per 15 s using the criteria proposed by Evenson and Puyau^45^

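### Baseline spread from September to mid-February, with follow-up 8–10 months later, lets season into the between-nursery variation and ICCs for activity; the size is unknown and the point is minor

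*Protocol article*

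**What the plan says.** The Trial status section of the protocol article says that "baseline data collection started in September 2015 and will be completed by mid-February 2016". The Outcomes section places follow-up "8–10 months after the baseline (T1").

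Each time point is a short snapshot. For activity, "Accelerometers will be worn for 5 days including week and weekend days". For the nursery environment, "The EPAO consists of a 1-day observation" together with a review of documents. The Introduction states that "being outdoors is one of the most powerful correlates of physical activity in children".

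The Sample size section gives the between-nursery quantities a purpose: "The choice of 12 nurseries will provide some information on variability within and between nurseries at baseline and follow-up", and "the sample will indicate the likely response rates and intracluster correlations (ICCs) in anticipation of a larger trial". It adds that ICCs from other, adequately powered trials will also be used, and that the sample will not give a usefully precise effect estimate.

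Under Randomisation, nurseries are allocated after all of them have completed baseline, stratified by deprivation and location.

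**The concern.** If a nursery's children are measured within a few weeks of each other, time of year acts as a nursery-level factor. Two nurseries with the same underlying activity would then look different because one was visited in September and the other in December. With one short measurement period per time point, the data cannot separate that difference from a real difference between nurseries unless measurement date is used.

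What is at stake is a planning quantity. The ICC and the between-nursery SD for activity are named outputs that feed a larger trial. An ICC that carries season would make that trial larger than it needs to be if its own fieldwork is confined to one season. T0–T1 change within an arm also carries a seasonal part that varies by nursery.

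**Working it through.** The article gives no figure for this point, so there is none to reproduce. The check has four steps.

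**1. Calendar.** Inputs: baseline from September 2015 to 15 February 2016 (Trial status), which is 138 days from 30 September or 167 days from 1 September; T1 = T0 + 8, 9 or 10 months (Outcomes). An 8–10 month gap leaves T1 between 2 and 4 calendar months short of the anniversary of T0. September baselines return in May to July 2016. A 15 February baseline returns between 15 October and 15 December 2016.

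**2. Day length as a marker of season.** Latitude 51.6°N is assumed; day length comes from the standard solar declination formula.

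| Baseline | Day length at T0 (h) | Change at 8 / 9 / 10 months (h) |
|---|---|---|
| 1 Sept | 13.5 | +1.4 / +2.9 / +3.1 |
| 15 Sept | 12.6 | +3.1 / +4.1 / +3.6 |
| 1 Nov | 9.5 | +7.1 / +5.9 / +3.9 |
| 15 Dec | 7.8 | +6.7 / +4.6 / +2.6 |
| 15 Jan | 8.3 | +4.2 / +2.2 / +0.4 |
| 25 Jan | 8.7 | +3.1 / +1.1 / −0.4 |
| 1 Feb | 9.1 | +2.3 / +0.4 / −1.0 |
| 15 Feb | 9.9 | +0.6 / −1.2 / −2.1 |

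Baseline day length differs between nurseries by up to 13.5 − 7.8 = 5.7 h. The change at 9 months runs from +5.9 h to −1.2 h. The sign turns negative only for baselines from about late January, and only towards 9–10 months.

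**3. Effect on the ICC.** Let R be the seasonal swing across the baseline window in child-level SD units, spread evenly, so that its variance is R²/12. R is an assumption; the documents give no value. If all of it lies between nurseries,

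observed ICC = (ρ + R²/12) / (1 + R²/12).

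The design effect is 1 + 19 × ICC. Both ρ = 0.05 and 20 children per nursery are assumed.

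| R (SD) | R²/12 | Observed ICC | Design effect | Ratio to 1.95 |
|---|---|---|---|---|
| 0 | 0 | 0.050 | 1.95 | 1.00 |
| 0.25 | 0.0052 | 0.055 | 2.04 | 1.05 |
| 0.5 | 0.0208 | 0.069 | 2.32 | 1.19 |
| 1.0 | 0.0833 | 0.123 | 3.34 | 1.71 |

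The large-sample standard error of the ICC on the same inputs is (1 − 0.05) × (1 + 19 × 0.05) × √(2 / (20 × 19 × 11)) = 0.95 × 1.95 × 0.0219 = 0.041. The shifts of 0.005, 0.019 and 0.073 are therefore about 0.1, 0.5 and 1.8 standard errors.

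**4. Balance between arms.** Take 12 baselines evenly spaced from 1 September to 15 February (assumed), T1 at 9 months, and all 924 splits into 6 and 6. The arm difference in mean day-length change has expectation zero and SD 1.29 h; it exceeds 1 h in 47% of splits and 2 h in 13%. With a 30 September start the SD is 1.38 h and 49% exceed 1 h. These splits ignore the deprivation and location strata. In outcome units at baseline, the SD of the arm difference due to season is √(R²/12 × 2/6): 0.042, 0.083 and 0.167 SD for R = 0.25, 0.5 and 1.0.

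**The case against.** A good deal can be said for the plan.

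- **The absence of a season adjustment is not itself a defect.** The analysis plan and full protocol are not shown and may contain one. This stands; the point rests only on the timing that the article fixes.
- **Measuring a nursery's children together is not stated.** The Outcomes section speaks of multiple visits to each nursery, and the end of the window could be catch-up visits. Visits spread over months would put part of any seasonal effect within nurseries. This stands, so the ICC figures above are upper values for each R.
- **Day length is not activity.** The Introduction links activity to being outdoors, and nothing in the article converts daylight into minutes of activity. This stands; R is unknown.
- **The ICC will be imprecise in any case, and external ICCs will also be used.** This stands and lowers the severity. The trial's own ICC is still a named output, and a shift due to timing does not average out as sampling error does.
- **If the main trial also spreads fieldwork over seasons, seasonal variation belongs in its ICC.** This stands. Adjusting it away could then make that trial too small, and the fix allows for this.

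A reader might also infer more than the article supports:

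- **That season confounds the comparison of arms.** Allocation is random and follows all baseline collection, so baseline dates can differ between arms only by chance.
- **That the shift generally reverses between early and late nurseries.** Before about late January it has the same sign and differs only in size.
- **That every nursery is followed up in a different season.** A mid-February baseline with follow-up in mid-December is winter both times.
- **That the study will misread within-arm change as an effect.** The Analysis section plans descriptive summaries, and the Sample size section already disclaims a useful effect estimate. The primary outcomes concern acceptability, which these dates do not bias.

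**Conclusion.** The point holds in a limited form and is minor. The stated dates place nurseries at widely different times of year, with a T0–T1 seasonal shift of very unequal size. If each nursery is measured over a short period, part of any seasonal difference in accelerometer activity, and possibly in the outdoor-play content of EPAO, will be counted as variation between nurseries at T0 and T1.

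The effect is negligible for a swing of 0.25 SD (about 5% on the design effect), moderate at 0.5 SD (19%) and large at 1.0 SD (71%). The documents do not say which applies. These figures rest on an assumed true ICC of 0.05, 20 children per nursery and even spacing of visits. Between arms there is no systematic bias, but with 12 nurseries not balanced on date a sizeable chance imbalance is quite likely.

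**What to change.** 1. For accelerometer outcomes and EPAO, report the between-nursery SD or (where children are the units) the ICC at T0 and at T1 in two forms: unadjusted, and adjusted for measurement date through a single linear term for daylight hours in the measurement week. For planning, use the unadjusted value if the main trial will also spread its fieldwork over seasons, and consider the adjusted one if it will not.
2. At T1, interleave visits so that intervention and control nurseries within each location are measured in the same weeks, as far as the 8–10 month window allows. Because the EPAO assessor is blind to allocation, someone else should do the scheduling.

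The cost is small: visit dates only need to be kept with the data, and on the status date of 26 January 2016 all T1 visits still lay ahead. The downside is one degree of freedom among 12 nurseries, so the adjusted ICC is less precise and should stand beside the unadjusted one, not replace it.
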